##### Analysis

###### Power

Due to the staggered design, power was determined through simulation using the R (R Foundation for Statistical Computing) packages simstudy and lme [33]. For a varying number of participants, 1000 datasets reflecting the staggered design were generated, all assuming a normally distributed outcome variable, a correlation between consecutive weeks of Pearson *r*=0.8, and a final effect of Cohen *d*=0.5 between the baseline phase and the first week of the effect phase (increasing linearly in 6 weeks). With 24 participants, a significant intervention effect (*P*<.05) was observed in 80.3% (803/1000) of cases, between the measurements from the baseline phase and those from the effect phase. Assuming 22% dropout (based on the study by van Dam et al [17]), the study is adequately powered when a total of 24 + (0.22 × 24) = 30 participants are included.

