##### Effectiveness Study

Primary outcome data will be analyzed using a multilevel model (R, version 4.0+; package lme4) to investigate whether there is a significant difference between the level of professional care support moments (frequency or duration) per week in the baseline phase and the effect phase. The dependent continuous variable is the frequency and duration of professional care support moments per week. We will analyze all professional care support moments provided, as well as a selection of the specific professional care support moments connected to the goals for which the social robot is deployed.

The independent binary variable is the moment of measurement (baseline phase or effect phase). Because there are multiple measurements per participant at both phases, the model will contain a random intercept for participants. Time will be included in the model as a covariate. Measurements are consequently averaged and compared within participants per phase. Following the intention-to-treat principle, all participants will be included in the analysis, regardless of whether the participant has used the social robot in all weeks during the intervention adjustment phase and effect phase. Because multilevel models handle missing values well, no imputation is needed [34]. Quantitative secondary outcome data will be analyzed similarly. To assess the robustness of the primary outcome, additional per-protocol analyses and completers analyses will be performed as sensitivity analyses.

Clinical relevance will be determined per participant. Here, two conditions must be met as follows: (1) a Reliable Change Index of >1.96 for the level of support provided by care professionals [35] and (2) with CiSR, the participant progresses in carrying out the selected activities independently (GAS score of ≥+1 for at least one goal).

The follow-up data will be used to determine how many participants continue to receive CiSR, whether the effect is sustained in these participants, and what reasons there are to discontinue CiSR.

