For the analyses, R (version 4.0+; package lme4) will be used. Missing measurements will be handled using multiple imputations*.* Resource use and costs will be reported in means, SDs, and 95% CIs. Costs and outcomes will be measured at the baseline (CAU) and the effect and follow-up phases (CiSR). Baseline adjustments will be made if needed. Deterministic and probabilistic sensitivity analyses will be performed. Cost-effectiveness planes will be constructed by plotting the (bootstrapped) cost-effectiveness and cost-utility pairs. The likelihood that CiSR is a cost-effective option compared to CAU will be illustrated using a cost-effectiveness acceptability curve, which demonstrates the probability of an intervention being cost-effective for a given threshold. This represents the amount that society is willing to pay to gain one unit of effect. The willingness-to-pay threshold for the costs per reduced number of support moments is unknown, while the willingness-to-pay for a QALY varies across and within countries. In the Netherlands, the Health Council of the Netherlands estimated the QALY threshold between €20.000 and €80.000 (1=US $1.083; currency rate as per October 18, 2024) depending on the level of severity of the disease [40].

If, in practice, it appears that the data are of insufficient quality, making it impossible to create a model, the costs and effects will be described with a cost-consequence analysis.

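### No planned quantitative analysis tests informative dropout: the two named robustness checks only restrict the sample, and the intention-to-treat label supplies no effect-phase outcome for participants without an effect-phase diary

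*Protocol article*

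**What the plan says.** The primary model is set out in the Effectiveness Study part of the Analysis section. Its predictor has two levels: "The independent binary variable is the moment of measurement (baseline phase or effect phase"). The six adjustment weeks are therefore outside the contrast. The model has a random intercept per participant and time as a covariate. Imputation is declared unnecessary because multilevel models cope with missing values.

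The analysis is labelled intention-to-treat: "all participants will be included in the analysis, regardless of whether the participant has used the social robot in all weeks" of the adjustment and effect phases. This defines the set by use of the robot, not by whether effect-phase diaries exist.

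The robustness statement is: "To assess the robustness of the primary outcome, additional per-protocol analyses and completers analyses will be performed as sensitivity analyses". Neither set is defined in the article.

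The Power section finds 24 participants sufficient and inflates the number to 30: "Assuming 22% dropout". It does not say whether dropout means stopping the robot or leaving the study, or when it happens. Later in the analysis section, the visual-analysis paragraph promises a qualitative exploration of missing-data patterns and a discussion of what they mean for robustness.

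**The concern.** A participant who leaves during the six adjustment weeks, diary included, has baseline rows only. The model keeps those rows, so the person is formally included, but there is no observed change for them. The phase coefficient then rests on the people who stayed.

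That is harmless if leaving is unrelated to how support would have changed, given the data in the model. It is not harmless if people leave because the robot does not help them. The average among stayers would then be reported under an intention-to-treat label.

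The named checks would not reveal this. A completers analysis removes the baseline-only participants and leaves the same effect-phase data. A per-protocol analysis restricts the set in its own way. Neither changes the assumption about those who left, so agreement with the primary result could be read as confirmation when all three share the same selection.

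**Working it through.** **The plan's own figure.** 24 + 0.22 × 24 = 29.28, rounded up to 30, reproduces the stated total. (Dividing instead gives 24 / 0.78 = 30.77, so 31; the difference does not matter here.) With 30 enrolled, 22% is 0.22 × 30 = 6.6, about 7 people. The power percentage plays no part in this point.

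**Size by arithmetic.** Inputs from the Power section: effect 0.5 SD, dropout 22%. Assumptions: a fraction p has no effect-phase diary, and their true effect is k times that of stayers. The effect in all enrolled is 0.5 × [1 − p(1 − k)], while the analysis of available data targets 0.5. The overstatement factor is 1 / [1 − p(1 − k)].

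| p | k | Effect in all enrolled | Factor |
|---|---|---|---|
| 0.22 | 0 | 0.5 × 0.78 = 0.39 | 1.28 |
| 7/30 | 0 | 0.5 × 23/30 = 0.383 | 1.30 |
| 0.22 | 0.5 | 0.5 × 0.89 = 0.445 | 1.12 |
| 0.11 | 0 | 0.5 × 0.89 = 0.445 | 1.12 |
| any | 1 | 0.50 | 1.00 |

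**Does the planned model behave this way?** Simulation of the staggered design: 30 participants, 13 weeks, baselines of 2 to 5 weeks, linear rise over six weeks to 0.5 SD, 600 datasets per scenario. Seven participants have zero effect and baseline diaries only. The article gives a correlation of 0.8 between consecutive weeks but not its structure, so AR(1) and exchangeable were both run. The true mean effect is 0.383.

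| Correlation | Time in model | All diaries kept | Planned model | Completers | Correlation, planned with completers |
|---|---|---|---|---|---|
| AR(1) | no | 0.367 | 0.479 | 0.478 | 0.99 |
| AR(1) | yes | 0.413 | 0.532 | 0.538 | 0.94 |
| Exchangeable | no | 0.387 | 0.501 | 0.501 | 0.995 |
| Exchangeable | yes | 0.392 | 0.506 | 0.503 | 0.94 |

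The rows with time match the plan. The planned model exceeds the full-diary result by 0.532 − 0.413 = 0.119 and 0.506 − 0.392 = 0.114 SD. On average, planned and completers estimates differ by less than 0.01 SD.

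**What baseline-only participants contribute.** With time in the model and dropout unrelated to effect, the standard error is 0.470 with them and 0.514 without (AR(1)), or 0.289 and 0.308 (exchangeable). They help to estimate the time slope, but say nothing about their own change.

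**Possible remedies.** Setting the missing effect-phase weeks to the participant's own baseline mean gave 0.36 to 0.39, close to the truth. Entering the adjustment weeks as a third phase level did not work. Without time it moved the estimate only from 0.47 to 0.45. With the planned linear time term it brought the estimate to within about 0.06 SD of zero, because the slope absorbs the six-week rise.

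**The case against.** Several stronger readings are tempting, and the document does not support them.

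- *Everyone who stops the robot is lost.* The Primary Outcome section has staff log the diary for each participant throughout the research period, and the intention-to-treat sentence keeps people regardless of robot use. Read together, someone who stops the robot but still has a diary stays in the primary analysis. Only those without effect-phase diaries are affected, and the article does not say how many of the 22% that would be.
- *Early leavers add nothing.* With time in the model they add some precision, as shown above.
- *Dropout is not examined at all.* The qualitative review of missing data is planned, and each participant's adjustment weeks are graphed. What is lacking is a quantitative test.
- *The economic section contradicts the primary analysis.* It says "Missing measurements will be handled using multiple imputations", but this may mainly concern the cost and quality-of-life questionnaires. Different handling for different data is ordinary, and the economic model also draws on literature and expert opinion.

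The best remaining objection is that this is an article, and departures from missing at random are often left to a statistical analysis plan. That has weight: further analyses may exist elsewhere. It does not fully answer the point, because the article itself names the analyses meant to establish robustness, and those cannot do so for dropout. It is also fair that a shift of about 0.12 SD is only a quarter of the planned model's standard error under AR(1) (0.119 / 0.468 = 0.25).

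**Conclusion.** The point holds in a limited form. For participants without effect-phase diaries, the intention-to-treat label brings in no information on their change, and neither named robustness analysis can show whether their absence distorts the result.

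The overstatement would be about 28% to 30% if all 22% left before the effect phase and had no effect. It would be about 12% if they had half the effect, or if only half of them lacked effect-phase diaries and those had no effect. It would be nil if they responded like stayers. These rates of loss and response are assumptions; the article gives neither. A reader might infer that the primary estimate is biased. The document does not show that. It shows only that the planned quantitative analyses would not reveal such a bias if it occurred. This is a cheap improvement to the sensitivity analyses, not a defect that invalidates the primary model.

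**What to change.** 1. Add one quantitative sensitivity analysis of the primary outcome in which missing effect-phase weeks after dropout are centred on the participant's own baseline level, representing a return to care as usual. Use multiple imputation, or a delta-adjusted range running from that assumption to response like stayers. Do not simply fill in a fixed baseline mean: that treats assumed weeks as observed and understates the standard error.
2. Present the per-protocol and completers analyses as supplementary, not as the test of robustness.
3. Confirm in one sentence that diary weeks recorded after a participant stops using the robot enter the primary analysis.
4. Leave the primary model's two-level phase contrast as it is. Adding the adjustment weeks as a phase level alongside linear time would nearly erase the effect under the plan's own assumption of a linear rise.

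The cost is some wording and one extra model run, with no change to the design. The downside is that the reported effect may be smaller under the new analysis.

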##### Health Economic Evaluation

A model-based economic evaluation with a follow-up time equal to the life span of the social robot will be performed. This study will be reported by following the Consolidated Health Economic Evaluation Reporting Standards 2022 guidelines for reporting economic evaluations in health care [37]. This study will also follow the Dutch guideline for health economic evaluations [32].

If the collected data suffices, the cost-effectiveness of CiSR will be examined by a model-based economic evaluation. For this, a Markov model, following the established guidelines [32,38], will be developed. Costs and effects will be modeled for 5 years with cycles of 3 months. The sources for transition opportunities, effects, and cost data will be the effect study, scientific literature, and expert opinions. Cost estimates from the Dutch costing manual will be used as a reference. For costs and health outcomes that occur after 1 year, a 3% discount rate to future costs and a 1.5% discount rate to future health outcomes will be applied [32]. Cost prices will be expressed in euros based on the cost prices in 2024 (index year). If necessary, the existing cost prices will be updated to those in 2024 using the consumer price index available from Statistics Netherlands. Outcomes will be incremental cost-effectiveness ratios using societal costs and effects (the costs per reduced number of support moments), or incremental cost-utility ratios expressed in costs per quality-adjusted life years (QALYs). The QALYs will be calculated for the utilities obtained by the ICECAP-A [39].

For the analyses, R (version 4.0+; package lme4) will be used. Missing measurements will be handled using multiple imputations*.* Resource use and costs will be reported in means, SDs, and 95% CIs. Costs and outcomes will be measured at the baseline (CAU) and the effect and follow-up phases (CiSR). Baseline adjustments will be made if needed. Deterministic and probabilistic sensitivity analyses will be performed. Cost-effectiveness planes will be constructed by plotting the (bootstrapped) cost-effectiveness and cost-utility pairs. The likelihood that CiSR is a cost-effective option compared to CAU will be illustrated using a cost-effectiveness acceptability curve, which demonstrates the probability of an intervention being cost-effective for a given threshold. This represents the amount that society is willing to pay to gain one unit of effect. The willingness-to-pay threshold for the costs per reduced number of support moments is unknown, while the willingness-to-pay for a QALY varies across and within countries. In the Netherlands, the Health Council of the Netherlands estimated the QALY threshold between €20.000 and €80.000 (1=US $1.083; currency rate as per October 18, 2024) depending on the level of severity of the disease [40].

If, in practice, it appears that the data are of insufficient quality, making it impossible to create a model, the costs and effects will be described with a cost-consequence analysis.

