###### Quality of Life

To measure the participants’ quality of life, the Icepop Capability Measure for Adults (ICECAP-A) will be administered [30,31]. The use of this questionnaire is advised when performing a cost-effectiveness study [32]. The ICECAP-A contains 5 items measuring stability, attachment, autonomy, achievement, and enjoyment.

Table 2 shows an overview of the measurements.

**Table 2 table2:** Study measurements overview.

Measurement	Baseline	Intervention adjustment	Effect	Follow-up	Used to answer RQ^a^
Daily registration of support (diary)^b^	✓	✓	✓	✓	RQ1 and RQ2
Weekly evaluation of goals (GAS^c^)^b^		✓	✓	✓	RQ3
Interview: well-being (PWI-ID^d^)^b^	✓	✓	✓	✓	RQ4
Interview: psychosocial impact (PIADS-10^e^)^f^			✓	✓	RQ4
Interview: added value of CiSR^f,g^			✓	✓	RQ4
Interview: work engagement and added value of CiSR^h^			✓	✓	RQ3, RQ4, and RQ5
Questionnaire: work engagement^h^			✓	✓	RQ5
Questionnaire: medical consumption and productivity cost (iMCQ^i^+iPCQ^j^)^b^	✓		✓	✓	RQ6 and RQ7
Questionnaire: quality of life (ICECAP-A^k^)^b^	✓		✓	✓	RQ6 and RQ7

^a^RQ: research question.

^b^Information on individuals with challenges in daily structure and planning, provided by the care professional.

^c^GAS: goal attainment scaling.

^d^PWI-ID: Personal Wellbeing Index–Intellectual Disability.

^e^PIADS-10: 10-item Psychosocial Impact of Assistive Devices Scale.

^f^Information on individuals with challenges in daily structure and planning provided by the individuals themselves.

^g^CiSR: care involving a social robot.

^h^Information on care professional.

^i^iMCQ: iMTA Assessment Medical Consumption Questionnaire.

^j^iPCQ: iMTA Assessment Productivity Cost Questionnaire.

^k^ICECAP-A: Icepop Capability Measure for Adults.

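### QALYs are to be calculated from the ICECAP-A, a capability measure, with no stated mapping to health utility, and set beside a euro-per-QALY range

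*Protocol article*

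**What the plan says.** Three places in the protocol article bear on this.

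- **Quality of Life.** The instrument is introduced thus: "the Icepop Capability Measure for Adults (ICECAP-A) will be administered". Its content follows: "The ICECAP-A contains 5 items measuring stability, attachment, autonomy, achievement, and enjoyment". The reason given for choosing it is: "The use of this questionnaire is advised when performing a cost-effectiveness study", with a citation to the Dutch guideline for health economic evaluations (reference 32). Table 2 schedules it at baseline, effect and follow-up.
- **Health Economic Evaluation, outcomes.** Two types of ratio are planned, joined by 'or': cost per reduction in support moments, and "incremental cost-utility ratios expressed in costs per quality-adjusted life years (QALYs". For the second: "The QALYs will be calculated for the utilities obtained by the ICECAP-A", with reference 39 attached.
- **Health Economic Evaluation, acceptability curve.** Willingness to pay is explained as what society would give for one more unit of the effect in question. The article says that this value is not known for a support moment. For QALYs it says that "the Health Council of the Netherlands estimated the QALY threshold between €20.000 and €80.000", "depending on the level of severity of the disease".

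**The concern.** A QALY weights time by a value on a scale where 0 is dead and 1 is full health. Euro-per-QALY thresholds are expressed in that unit. An index built from stability, attachment, autonomy, achievement and enjoyment measures something else. Multiplied by time, it gives years weighted by capability.

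The article calls these values utilities and the product a QALY, and cites a per-QALY range graded by disease severity in the paragraph that sets up the acceptability curve. A funder reading the result would naturally set it beside cost-per-QALY figures for other programmes, although the two are not in the same unit. The Discussion names funding bodies and policy makers as intended users of the results.

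**Working it through.** The article gives no numerical result to reproduce. The main check is a comparison of its own statements.

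**1. Source of the weights.** The Health Economic Evaluation section names only the ICECAP-A. Table 2 has no health-utility questionnaire. The Personal Wellbeing Index–Intellectual Disability has a health domain, but Table 2 assigns it to RQ4 (well-being) and not to the economic evaluation.

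**2. Nature of the weights.** By its name the ICECAP-A measures capability, and none of the five listed items is a health item. The article gives no anchors, value set or index range, and no step that converts capability values to health utility.

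**3. The unit in the threshold.** The article ties willingness to pay to the unit of effect and concedes that there is no known value for a support moment. By the same reasoning a value for a capability-weighted year has to be stated separately, and none is. The plan has a euro range for this outcome only because the outcome is called a QALY.

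**4. Illustration of what depends on the missing exchange rate.** From the article: a 5-year horizon, 3-month cycles (20 cycles), 1.5% discounting of effects occurring after year 1, and €20,000 and €80,000 per QALY. Assumed here, not in the article: a sustained gain g on the ICECAP-A index, and an exchange rate k, the health utility that one unit of capability is worth.

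Discounted years: D = Σ 0.25 × d(i) for i = 1 to 20, with d(i) = 1 for i ≤ 4 and d(i) = 1.015^−(0.25i − 1) for i > 4. This gives D = 4.876. Discounting from time zero instead gives 4.809, so the convention matters little.

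Cost that the range would appear to justify per participant = g × k × D × threshold. For g = 0.05 and k = 1: 0.05 × 4.876 = 0.244 units; × €20,000 = €4,876; × €80,000 = €19,504.

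| Assumed gain g | Assumed k | At €20,000 | At €80,000 |
|---|---|---|---|
| 0.02 | 1 | €1,950 | €7,802 |
| 0.05 | 1 | €4,876 | €19,504 |
| 0.05 | 0.5 | €2,438 | €9,752 |
| 0.05 | 0.25 | €1,219 | €4,876 |
| 0.10 | 1 | €9,752 | €39,008 |

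The justified cost is proportional to k. Reading the ICECAP-A value directly as a utility amounts to setting k = 1, and the article gives no argument for that value.

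**The case against.** The strongest reply is that the decisive premise lies outside the article. It does not state how the ICECAP-A is anchored, and it cites two sources: reference 39 for the QALY calculation and reference 32 for the choice of questionnaire. Either could contain a justification, and a condensed article may leave a scoring or mapping step to the full protocol. This stands as a limit. A reader might infer that no QALY could ever be derived from these data; the article does not support that, because a mapping may exist in material not shown. It does not remove the point, however. The article positively states how the QALYs will be obtained, and the sentence on reference 32 says only that the questionnaire is advised for cost-effectiveness studies, not that it yields QALY weights.

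A second reply concerns reach. A reader might infer that every statement on the robot's cost-effectiveness would be in the wrong unit. That goes too far. Cost per reduced support moment is a separate outcome with its own cost-effectiveness pairs. The model is conditional on sufficient data, with a cost-consequence analysis as fallback.

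Third, a reader might infer that the plan commits to a decision against the €20,000 to €80,000 range. No such rule is written. The range is given as context, beside a remark that willingness to pay for a QALY differs between and within countries. Its use in interpretation is a natural inference from where it stands, not a stated rule.

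Finally, the euro figures rest on an assumed gain and assumed exchange rates. They do not measure how far the result would be from a correct one.

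**Conclusion.** The concern holds for the cost-utility branch of RQ6. The article fixes a calculation that labels capability-weighted years as QALYs, and sets beside them a range expressed in a different unit. This is a stated rule that does not fit the instrument described, not a detail left to a fuller document.

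Neither the size nor the direction of any error can be given. The illustration shows only that the apparently acceptable cost scales one-for-one with an exchange rate the article does not supply.

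The conclusion rests on general knowledge of the method (a QALY weight is anchored at dead and full health; a capability index at no and full capability). The instrument's name and item list agree with this but do not prove it. It also assumes that no mapping exists in the full protocol or in references 32 and 39, which could not be checked.

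The support-moment ratio and its acceptability curve, the cost-consequence fallback and RQ1 to RQ5 are unaffected. The matter should be corrected before the economic results are reported, but it does not threaten the trial.

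**What to change.** In Health Economic Evaluation:

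1. Name the ICECAP-A outcome years of full capability (capability-weighted years), and report the incremental cost per such year in place of cost per QALY.
2. Show the acceptability curve for this outcome over a range of willingness-to-pay values, and do not interpret it against the €20,000 to €80,000 per-QALY range.
3. Alternatively, if a cost-per-QALY result is to be kept, state the mapping from the ICECAP-A to health utility and justify it.

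The first two changes are text only and need no new data. Their cost is the loss of a direct comparison with the national QALY threshold, which the planned measurements do not support without a mapping.

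Adding a health-utility questionnaire now is not a practical alternative. In the economic evaluation, care as usual is measured only at baseline, and 29 of the 30 planned participants were enrolled by October 2024. A late addition would therefore have few or no care-as-usual values from which to form an increment.
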